#### Planned statistical analysis

Analyses are performed using the software packages R 3.2.1 and STATA 13, or later versions. The data analyst will be blinded to allocation arm. Analysis and presentation of data will be in accordance with the CONSORT guidelines, in particular the extensions to pragmatic trials [76] and nonpharmacologic interventions [77]. Standard descriptive statistics (means, medians, ranges, standard deviations, frequencies, and percentages) will be used to report demographics, and baseline and outcome scores. Data will be examined for missing data and multiple imputation strategies will be used if necessary. Missing data are, however, expected to be low as data are collected through home interviews and the families are compensated.

Primary and secondary outcomes will be analyzed using multiple regression for continuous outcomes, and logistic regression for binary outcomes controlling for baseline scores where possible. A two-tailed test  $\alpha = 0.05$  will be used and parameters will be summarized using 95 % confidence intervals. If assumptions for parametric analysis are not met, non-parametric tests like the Mann-Whitney *U* test will be used. To account for group or therapist effects, standard errors will be clustered around the group for the parents in the intervention arm.

Analysis will follow intention-to-treat (ITT) principles, but completer analysis (such as complier average causal effects (CACE) based on treatment received will also be performed. To examine how non-compliance affects results two levels of participation will be explored: parents that have participated in at least three of the eight

sessions, and parents that have participated in at least six of the eight sessions.

As larger effects are expected in parents who present difficulties at the time of recruitment, separate analysis will be carried out for the following three groups: parents who have baseline scores in the clinical range of the measures, parents who are scoring within the lowest 25 % of the distribution at baseline, parents who are scoring within the lowest 50 % of the distribution at baseline.

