## Inclusion criteria

Mothers with infants aged up to four months who are able to read and write Danish may be included in the trial. In Ikast-Brande, only primiparous (that is, have

[figure not shown]

given birth for the first time) mothers are invited; in Herning primi- and multi-parous mothers living in certain districts of the city are invited.

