### **Randomization**

An independent researcher computes a random allocation list stratified by municipality and with a block size of three. The allocation ratio is 2:1 (IYPB:UC), as it is important for the municipalities to have enough families in the IYPB intervention arm to start the groups. After the baseline assessment is completed, the interviewer informs a designated research

administrator that the interview has been completed. The research administrator then randomizes the family by adding the name to the randomization list in the order the names arrive from the interviewer. Then the contact person in the municipality is informed about the allocation status of the family. Participants are informed by their health visitor as to which arm of the study they have been allocated to. In the case where consent to treatment is withdrawn but the participant agrees to remain in the research study, the participant is followed to completion.

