### Background questions

Background questions and socio-demographics are collected at T1, T2, and T3. They measure parent age, education, occupation, ethnicity, number of children, household status, housing situation, household economy, substance abuse, child birth weight, child gestation at birth, and child health.

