### Data analysis

#### Sample size

Lancaster *et al.* [75] recommended that the sample size of a pilot study be a minimum of 30 participants to be able to estimate parameters. As a small effect size is expected with a universal sample, the size of the pilot trial is 128 mothers. With a sample size of 128, a power of 0.8, and a two-sided alpha level of 0.05, it is possible to detect an effect size of 0.50 (Cohen's *d*).

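### The stated regression leaves out municipality, the randomisation stratifier, so reported standard errors will be slightly too large if municipality predicts outcome; adding it is a free improvement

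*Protocol*

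**What the plan says.** Protocol, Randomization: allocation is 2:1, from "a random allocation list stratified by municipality and with a block size of three".

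Protocol, Inclusion criteria: Ikast-Brande invites first-time mothers only, whereas "in Herning primi- and multi-parous mothers living in certain districts of the city are invited".

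Protocol, Planned statistical analysis: continuous outcomes are analysed by multiple regression and binary outcomes by logistic regression, "controlling for baseline scores where possible". No other covariate is named. The only other design feature carried into the analysis is clustering of standard errors by parent group in the intervention arm.

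Protocol, Primary outcomes and Table 1: KPCS is measured at T1 and T2. PSS is measured at T2 and T3 only, so it has no baseline score. BaM-13, PRFQ-1, PSOC, SDQ, CDQ, MABISC and the video also have no T1 measurement.

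Protocol, Background questions: "Background questions and socio-demographics are collected at T1, T2, and T3". The list includes number of children.

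**The concern.** When randomisation is stratified, the arms are balanced on the stratifier by design. If the stratifier also predicts outcome, the treatment estimate varies less from trial to trial than an analysis without the stratifier assumes. The residual variance then contains a between-municipality component that does not contribute to the error of the treatment comparison. The reported standard error is too large, the confidence interval too wide, and the test conservative.

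There is reason to think municipality may be prognostic here. The strata have different parity rules, and the primary constructs are parenting confidence and parenting stress, on which previous experience as a parent may well bear. The baseline score could absorb part of this for KPCS. For PSS and the other measures without a T1 score, the model as stated is an unadjusted two-group comparison.

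Two things are at stake. One is a small amount of power in a trial with little to spare. The other is the variance estimate that the pilot is meant to hand on to a definitive trial, which would be somewhat inflated if taken from a model without the stratifier.

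**Working it through.** **Inputs from the protocol.** N = 128, power 0.80, two-sided alpha 0.05, d = 0.50 (Sample size); 2:1 allocation, hence about 85:43, stratified by municipality in blocks of three (Randomization).

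**Inputs assumed.** The protocol gives neither the outcome difference between municipalities nor the split of the sample. I take gaps g of 0 to 0.8 within-municipality SD and, unless stated, equal strata (p = 0.5). Clustering by parent group is left aside.

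**1. The plan's own figure.** The Sample size section claims that, at these settings, "it is possible to detect an effect size of 0.50".
- Equal allocation, normal formula: n per arm = 2(1.960 + 0.842)²/0.50² = 62.8, so 63 per arm and 126 in total. The t-test version gives 64 per arm, 128 in total, power 0.801. The stated figure reproduces at 1:1.
- At 85:43 the standard error in SD units is sqrt(1/43 + 1/85) = 0.1871. Power = Φ(0.50/0.1871 − 1.960) = Φ(0.712) = 0.762 (t-test 0.755). This is the reference for what follows.

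**2. Effect of omitting municipality.** With residual variance 1 within municipality, omission raises the residual variance to 1 + p(1−p)g². The reported standard error is multiplied by sqrt(1 + p(1−p)g²). Power below is Φ(0.50/(factor × 0.1871) − 1.960).

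| Gap g (SD) | SE factor, p = 0.5 | Power at d = 0.50 | Loss from 0.762 (points) | SE factor, p = 0.3 |
|---|---|---|---|---|
| 0 | 1.000 | 0.762 | 0 | 1.000 |
| 0.2 | sqrt(1.0100) = 1.005 | 0.758 | 0.4 | 1.004 |
| 0.3 | sqrt(1.0225) = 1.011 | 0.753 | 0.9 | 1.009 |
| 0.5 | sqrt(1.0625) = 1.031 | 0.736 | 2.5 | 1.026 |
| 0.8 | sqrt(1.1600) = 1.077 | 0.699 | 6.3 | 1.065 |

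**3. Simulation.** 4,000 trials per setting, N = 128, 2:1, blocks of three within two equal strata, no baseline covariate (the PSS case), least squares without and with municipality:

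| Gap | Mean reported SE, d = 0.50 (without / with) | True spread of estimate, d = 0.50 (without / with) | Type I error (without / with) | Power, d = 0.50 (without / with) |
|---|---|---|---|---|
| 0.2 | 0.1886 / 0.1877 | 0.1890 / 0.1890 | 0.052 / 0.052 | 0.751 / 0.754 |
| 0.5 | 0.1929 / 0.1871 | 0.1880 / 0.1880 | 0.047 / 0.055 | 0.736 / 0.756 |
| 0.8 | 0.2019 / 0.1872 | 0.1847 / 0.1844 | 0.033 / 0.047 | 0.703 / 0.759 |

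The true spread of the estimate is essentially the same either way. Only the reported standard error, and with it the rejection rate, changes. The simulation error of a type I rate near 0.05 is about sqrt(0.05 × 0.95/4000) = 0.003, so only the drop to 0.033 is clearly outside noise.

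**4. KPCS, which has a baseline.** Assume a baseline–outcome correlation of 0.5 and the same gap at T1 and T2. The gap left after adjustment is g(1 − 0.5)/sqrt(1 − 0.25).
- g = 0.3: 0.15/0.866 = 0.17, SE factor 1.004.
- g = 0.5: 0.25/0.866 = 0.29, SE factor 1.010.

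This is about a third of the unadjusted inflation. It depends on the gap being present at T1. If the gap arose only after baseline, g = 0.5 would become 0.5/0.866 = 0.58 and the factor 1.041.

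**5. Variance passed on.** At g = 0.5 a residual variance taken from the model without municipality is 1.0625 times the within-municipality variance, about 6% too large.

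**The case against.** The strongest case against is that a protocol often leaves the full covariate list to the statistical analysis plan, which is not shown, and that the sentence does not say baseline scores are the only covariates. That is fair as far as it goes: nothing forbids adding municipality later. But the section does state a covariate rule, and following it as written omits the stratifier.

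The second objection is size. For modest gaps the effect is small, it errs on the safe side, and the documents do not show that municipality is prognostic. This stands, and it limits the point to an improvement.

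Four stronger readings are tempting, and the documents do not support them.
- **Bias, or confounding by parity.** Municipality and parity are only partly associated, since Herning also enrols first-time mothers. Arms are balanced within municipality, so the treatment effect is not confounded.
- **A less precise estimate.** Step 3 shows the true spread is unchanged when municipality is omitted. The loss is in the reported standard error and the test.
- **Parity and infant age must be in the model.** Neither is a stratifier, so there is no mismatch between design and analysis. Chance imbalance in them is already allowed for by the confidence interval, and the documents do not show how strongly either predicts outcome.
- **Adjustment recovers most or all of what 2:1 allocation costs.** The detectable effect rises from 0.50 to 0.528, a loss of 0.028. If covariates explained 5% of variance it would be 0.528 × sqrt(0.95) = 0.515, recovering 0.013 of 0.028, just under half. Near-full recovery needs 10% (0.528 × sqrt(0.90) = 0.501). Neither percentage has a source in the protocol, and for KPCS the baseline may already absorb part of it.

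**Conclusion.** The point holds in a limited form. The stated model does not carry the trial's own stratifier, and for PSS it carries no covariate at all. If municipality predicts outcome, reported standard errors are slightly too large and tests slightly conservative. There is no bias and no inflated type I error.

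For assumed gaps of 0.2 to 0.5 SD the inflation is about 0.5% to 3%, costing at most about 2.5 power points. A gap of 0.8 SD would cost about 8% and 6 points. KPCS is affected less where the gap already shows at T1, and at a gap of zero nothing is lost. These sizes rest on assumed gaps and equal strata; a 30:70 split gives slightly smaller figures. This is a free improvement and does not threaten the trial's conclusions.

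**What to change.** In Planned statistical analysis, state that the models for continuous outcomes include municipality as a fixed covariate alongside the baseline score where one was measured. For PSS and the other outcomes without a T1 score, municipality would then be in the model on its own. Do the same for binary outcomes where event counts allow. With about 43 controls, sparse events could make a logistic model unstable, and a covariate also changes the conditional odds ratio being estimated.

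Parity (from number of children at T1) and infant age at T1 may be added as prognostic covariates. They are optional and, if used, should be named before the data are analysed.

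The cost is one sentence and one degree of freedom per linear model, or three if both optional covariates are taken up as single terms. No new data are needed: municipality is on the randomisation list, number of children is already collected, and infant age is needed to check eligibility.

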## Abstract

**Background:** Infancy is an important period in a child's life, with rapid growth and development. Early experiences shape the developing brain, and adverse experiences can have both an immediate and lifelong impact on health and wellbeing. Parenting interventions offered to parents of newborns can support parents in providing sensitive and responsive care, and reinforce healthy development for their infants. This study aims to evaluate the impact of the Incredible Years™ Parents and Babies Program in a universal setting for parents with infants.

**Methods/Design:** This is a pragmatic, two-arm, parallel, pilot, randomized controlled trial (RCT) where 128 families with newborn infants up to four-months-old are recruited in two municipalities in Denmark. Families are randomized to the Incredible Years Parents and Babies Program or usual care with a 2:1 allocation ratio. The primary outcome is parenting confidence measured after 20 weeks by the Karitane Parenting Confidence Scale and Parental Stress Scale. Secondary outcomes include measures of parent health, reflective functioning, relationship with the infant, and infant development. Interviewers and data analysts are blind to allocation status.

**Discussion:** This is the first RCT of the Incredible Years Parents and Babies Program, and one of the first rigorous evaluations of a universally offered preventive intervention for parents with infants. The trial will provide important information on the effectiveness of a relatively brief, universally offered parenting intervention for parents of infants, and will also provide information on infant measures, parent recruitment and participation, and implementation of the program, which could inform future trials.

**Trial registration:** This trial was registered with Clinicaltrials.gov (identifier: NCT01931917) on 27 August 2013.

**Keywords:** Parenting, Parenting interventions, Early intervention, Early childhood, Infants, Incredible Years™, Randomized controlled trial, Universal intervention, Prevention

Correspondence: [contact]

SFI - The Danish National Centre for Social Research, Department for Children and Family, [name]

University of Copenhagen, Department of Public Health, [name]

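### Randomisation is stratified by municipality but the stated covariate rule names only baseline scores, so the linear models may slightly overstate the standard error, most clearly for PSS

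*Protocol*

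**What the plan says.** Protocol, Randomization: "An independent researcher computes a random allocation list stratified by municipality and with a block size of three", with allocation 2:1 in favour of the programme.

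Protocol, Inclusion criteria: Ikast-Brande invites only first-time mothers, while "in Herning primi- and multi-parous mothers living in certain districts of the city are invited".

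Protocol, Planned statistical analysis: "Primary and secondary outcomes will be analyzed using multiple regression for continuous outcomes, and logistic regression for binary outcomes", "controlling for baseline scores where possible". The same section adds that "standard errors will be clustered around the group for the parents in the intervention arm". Municipality is not named as a covariate there.

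Protocol, Abstract: "The primary outcome is parenting confidence measured after 20 weeks by the Karitane Parenting Confidence Scale and Parental Stress Scale". Table 1 and the outcome descriptions show KPCS at T1 and T2, and PSS at T2 and T3 only.

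**The concern.** Stratified blocks keep the arms balanced on municipality. A difference in outcome level between municipalities therefore cancels out of the treatment contrast and does not add to its true sampling variance. A linear model gets the benefit only if it contains the stratum. Without it, the between-municipality variance stays in the residual and the reported standard error is larger than the design warrants.

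There is some reason to expect a difference, because the strata admit mothers with different parenting experience and the primary outcomes concern parenting confidence and stress. The protocol does not say how large it is.

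KPCS has its own T1 score, which would carry part of any municipality difference. PSS has none, so it is the primary outcome with most to lose. At stake is a modest amount of precision, and agreement between how the trial is randomised and how it is analysed.

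**Working it through.** **Inputs from the protocol.** Two strata, blocks of three, 2:1 allocation (Randomization); 128 mothers, two-sided alpha 0.05 (Sample size).

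**Assumptions, because the protocol gives neither figure.** D is the outcome difference between municipalities in within-municipality SDs; p is the share of families in one municipality.

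**The plan's own figure.** The protocol states that 128 mothers give power 0.80 for d = 0.50. A two-sample t calculation gives 0.801 at 64:64 and about 0.755 at 43:85. The effect of the 2:1 ratio on that statement is a separate matter; it only explains why the powers below start near 0.755.

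**Formula.** With within-municipality SD 1, the total variance is 1 + p(1−p)D². Because the arms are balanced on municipality,

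SE without municipality / SE with municipality = √(1 + p(1−p)D²).

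For p = 0.5:

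- D = 0.2: √(1 + 0.25 × 0.04) = √1.0100 = 1.005, or 0.5% too wide
- D = 0.3: √(1 + 0.25 × 0.09) = √1.0225 = 1.011, or 1.1%
- D = 0.5: √(1 + 0.25 × 0.25) = √1.0625 = 1.031, or 3.1%

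For p = 0.3 the figures are 0.4%, 0.9% and 2.6%. For D = 0 the ratio is 1.

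**On the outcome scale.** With 43 and 86 families, the SE within municipality is √(1/43 + 1/86) = 0.187 SD. At D = 0.5 and p = 0.5 the model without municipality reports 0.187 × 1.031 = 0.193. The 95% half-width goes from about 0.37 to 0.38 SD.

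**Simulation check.** 129 families in two municipalities of nearly equal size, stratified 2:1 blocks of three, no baseline covariate, ordinary model-based standard errors, 8,000 runs per setting. Power is at a treatment effect of 0.5; SEs and type I error are from the runs with no effect.

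| D | SE without | SE with | Power without | Power with | Type I without | Type I with |
|---|---|---|---|---|---|---|
| 0 | 0.186 | 0.186 | 0.755 | 0.756 | 0.052 | 0.052 |
| 0.2 | 0.188 | 0.187 | 0.755 | 0.757 | 0.045 | 0.047 |
| 0.3 | 0.188 | 0.186 | 0.745 | 0.751 | 0.051 | 0.054 |
| 0.5 | 0.192 | 0.186 | 0.735 | 0.755 | 0.041 | 0.048 |

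The actual spread of the estimate stayed between about 0.186 and 0.189 throughout, whatever D was. Only the reported SE moved. At an extreme D of 0.75 the inflation is 6.8% and power is 0.717 against 0.763.

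**Limits.** These figures are for linear models without a baseline score. A baseline score, as for KPCS, shrinks them. They do not carry over to logistic models, where leaving out a prognostic factor mainly moves the odds ratio toward the null.

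**The case against.** The best reply is that the text excludes nothing. It says baseline scores in the plural, without limiting them to the outcome's own score. KPCS, MDI10, WHO-5, SOC13 and ASQ-SE are all measured at T1 and could enter the PSS model. A statistical analysis plan that is not shown might list municipality. The loss is also small, conservative in direction, and rests on an assumed difference, in a pilot trial.

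Most of this stands. It rules out saying that PSS will be analysed with no covariate; what can be said is that PSS has no T1 score of its own. It also keeps the point small. It does not remove it: the protocol does state a covariate rule, and that rule leaves out the one factor the allocation is built on. Clustering standard errors on parent groups in one arm does not replace a municipality term.

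Some stronger readings are tempting but unsupported:

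- A reader might infer that unequal dropout between municipalities would bias the result. If loss is equal in both arms, the arms stay balanced on municipality. Bias would need loss that differs by arm within municipality, and nothing in the protocol suggests that; it expects little missing data.
- A reader might take the Cost section as evidence that usual care differs. It only plans, if possible, to calculate average costs by municipality, and the Control section describes one usual care.
- A reader might want parity treated the same way. Parity is not a stratification factor, and chance imbalance in it is not a design error; ordinary intervals already allow for it.
- A reader might expect the clustered standard errors to enlarge the loss. That depends on parent groups being formed within one municipality, which the protocol does not state.

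**Conclusion.** The point holds as a modest matter of precision and consistency. The linear models as described may report standard errors that are slightly too large: about 0.5% to 3% for equal-sized municipalities differing by 0.2 to 0.5 SD, with a power loss of up to about 2 points. Both the difference and the split are assumptions, and the loss is zero if municipality does not predict the outcome. The error is on the conservative side and does not threaten the validity of the test. PSS is the most exposed primary outcome, KPCS less so.

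**What to change.** In Planned statistical analysis, add a sentence such as: *All regression models for primary and secondary outcomes include municipality as a fixed effect, together with the baseline score where it was measured.* If a separate analysis plan already says this, bring the protocol into line with it.

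The cost is one sentence and one degree of freedom. Municipality is known for every family at randomisation, so no new data are needed. Fixing it in advance also removes any later choice between adjusted and unadjusted results.

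### The only non-parametric fallback named, the Mann-Whitney test, cannot keep the baseline adjustment, group clustering or effect estimate that the same paragraph requires

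*Protocol*

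**What the plan says.** All the rules stand in one paragraph of the Protocol, Planned statistical analysis:

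- Continuous outcomes go into multiple regression and binary outcomes into logistic regression, "controlling for baseline scores where possible".
- Results are reported as estimates: "parameters will be summarized using 95 % confidence intervals".
- The fallback: "If assumptions for parametric analysis are not met, non-parametric tests like the Mann-Whitney" U test will be used.
- For group or therapist effects, "standard errors will be clustered around the group for the parents in the intervention arm".

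Two other places rely on an effect estimate. Aim 1, at the end of the Background, is to estimate effects and supply parameters for a later definitive trial. The Cost section measures benefit in natural units of the primary parenting measures.

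Under Primary outcomes and Table 1, KPCS is measured at T1 and T2. PSS is measured at T2 and T3 only.

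**The concern.** If the fallback is followed with the test it names, three neighbouring rules cannot be met. A Mann-Whitney test has no place for a baseline covariate. It has no regression standard error to cluster. It gives a statement about ranks, not an adjusted mean difference with a confidence interval.

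The fallback could apply to some outcomes and not others. Results for different scales would then rest on different quantities. For an affected primary outcome there would be no coefficient to carry into the definitive trial or the cost-effectiveness ratio. The outcomes are bounded item sums in a universal sample, so some skew is plausible and the rule could well come into play.

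**Working it through.** **1. Inputs.** From the Protocol: N = 128, two-sided alpha 0.05, power 0.8 and d = 0.50 (Sample size); 2:1 allocation, taken as 85 IYPB and 43 usual care (Randomization); groups of six to eight parents, taken as 7 (Intervention). Not given, so assumed: ICC within IYPB groups of 0 to 0.20, and baseline-outcome correlation r of 0.5, or 0 where no baseline exists.

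**2. The plan's own figure.** For the N, power and alpha listed in step 1, the Sample size section claims: "it is possible to detect an effect size of 0.50". At 1:1, n per arm = 2(1.96 + 0.842)²/0.50² = 62.8, so 63 per arm and 126 in all; an exact t-test with 64 per arm has power 0.801. The figure therefore reproduces for 1:1, unclustered and unadjusted. At 85:43 the t-test power is 0.755. That is a separate matter and serves here only as a reference.

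**3. Requirements against the named test.**

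| Requirement in the paragraph | Regression | Mann-Whitney U |
|---|---|---|
| Baseline adjustment where possible | yes | no |
| Standard errors clustered on IYPB group | yes | no |
| Regression parameter with 95% CI | yes | no |

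Outcomes with a T1 value (KPCS, MDI10, WHO-5, ASQ-SE) lose all three. PSS and others without a T1 value lose the last two.

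**4. Type I error when groups are ignored (analytic).** The design effect in the IYPB arm is 1 + (7 − 1) × ICC. The assumed variance is v0 = 1/85 + 1/43 = 0.03502; the true variance is v = DE/85 + 1/43. Actual alpha = 2[1 − Φ(1.96 × √(v0/v))].

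- ICC 0.05: DE 1.3, v/v0 = 1.101, alpha 6.2%
- ICC 0.10: DE 1.6, v/v0 = 1.202, alpha 7.4%
- ICC 0.20: DE 2.2, v/v0 = 1.403, alpha 9.8%

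**5. Power at ICC 0 (analytic, normal data, exact 2:1).** SE = √(1/85.33 + 1/42.67) = 0.1875. For regression with r = 0.5, the residual SD is √(1 − 0.25) = 0.866, so power = Φ(0.50/(0.866 × 0.1875) − 1.96) = Φ(1.119) = 0.868. For Mann-Whitney, with asymptotic efficiency 0.955, power = Φ(√0.955 × 0.50/0.1875 − 1.96) = Φ(0.646) = 0.741.

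**6. Simulation (4000 replicates per cell, normal data).** Controls are single-member clusters and the cluster-robust t-test has (clusters − 1) degrees of freedom. Each cell shows regression / Mann-Whitney.

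| ICC | Power, r = 0.5 | Null rejection, r = 0.5 | Power, r = 0 | Null rejection, r = 0 |
|---|---|---|---|---|
| 0 | 0.86 / 0.73 | 5.0% / 4.8% | 0.75 / 0.74 | 4.9% / 4.7% |
| 0.05 | 0.82 / 0.72 | 5.4% / 5.8% | 0.70 / 0.71 | 4.6% / 4.9% |
| 0.10 | 0.77 / 0.73 | 5.4% / 7.8% | 0.68 / 0.72 | 5.6% / 7.2% |
| 0.20 | 0.71 / 0.71 | 5.9% / 9.6% | 0.61 / 0.70 | 6.7% / 10.2% |

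The Monte Carlo standard error is about 0.004 for null rejection and 0.005 to 0.008 for power, so the simulated 7.8% agrees with the analytic 7.4%. Repeat runs differed from these powers by up to about 0.02. Where Mann-Whitney's null rejection exceeds 5%, its power is not at a true 5% level and is flattered by the comparison.

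**7. Non-normal outcomes (simulated, r = 0.5, regression / Mann-Whitney).** These are the cases the fallback is meant for.

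- Ceiling-bounded score: 0.81 / 0.72 at ICC 0; 0.73 / 0.70 at ICC 0.10.
- Strong lognormal-type skew: 0.68 / 0.73 at ICC 0; 0.66 / 0.71 at ICC 0.05. The ordering reverses.

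**The case against.** The Protocol offers Mann-Whitney as an example, and the clustering sentence comes after it. Rank regression, permutation or bootstrap methods that keep the covariate and the groups are not excluded. A reader might infer that the plan contradicts itself irreconcilably; the wording does not support that. What stands is that the only test named fails all three requirements and nothing says how a substitute should meet them.

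A reader might also infer that the fallback always costs power. It does not. With no baseline, as for PSS, the two methods have nearly the same power on normal data at ICC 0. Under strong lognormal-type skew Mann-Whitney does better. The gap of 0.86 against 0.73 belongs to normal data, r = 0.5 and ICC 0.

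A third tempting reading is that the primary test would be picked to suit the result. The analyst is blinded to allocation (Blinding; Planned statistical analysis), which limits steering. Which diagnostics trigger the switch is detail that a statistical analysis plan may supply, so its absence here is not part of this point.

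Finally, this is an external pilot, the fallback is conditional, and at ICC 0.05 the type I inflation is small. All of that limits the size of the problem. The pilot status also cuts the other way, because estimating effects is its first aim.

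**Conclusion.** The point holds as a defect in a stated rule: applied with the named test, the fallback defeats three requirements of its own paragraph and removes the estimate that aim 1 and the cost-effectiveness analysis need. That part rests on no assumption beyond the text.

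The numerical harm is moderate and conditional. For a KPCS-like outcome with r = 0.5, the power loss is about 0.13 on normal data at ICC 0 and about 0.10 at ICC 0.05. For a ceiling-bounded score it runs from 0.09 at ICC 0 down to 0.03 at ICC 0.10, and it becomes a gain under strong lognormal-type skew. For PSS no loss from baseline adjustment can be claimed. Type I error rises materially only if ICC is about 0.10 or more. The ICC, the correlation and the shape of the outcomes are all assumed. The plan should be changed, but the flaw does not invalidate the trial.

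**What to change.** Replace the fallback sentence with a rule of this kind: the regression, adjusted for the baseline score where one exists and with standard errors clustered on IYPB group, is the primary analysis for every continuous outcome. If residuals are clearly non-normal, a cluster bootstrap 95% confidence interval is reported for the same coefficient. Any rank-based analysis is a sensitivity analysis only and keeps the baseline covariate and the group clustering.

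The bootstrap should resample whole groups in the IYPB arm and individual mothers in usual care. With 85 mothers in groups of six to eight there are only about 11 to 14 groups (85/8 = 10.6; 85/6 = 14.2), so its interval should be read with that in mind.

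The cost is one sentence and slightly more analysis work. The real downside is possibly lower power than a rank test if an outcome proves very strongly skewed; the sensitivity analysis would show whether the conclusion depends on this.
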